#### Self-report measures

2.3.3.

The study staff administers the following validated, self-report questionnaires at baseline prior to randomization and at approximately 12 weeks (+/− 2 weeks) after baseline. Participants are given a four-week time frame surrounding the 12-week time point to complete the measures. This window, which has consistently been used by our research group, allows for greater flexibility for participants to complete these measures given their degree of medical morbidity. These measures can be administered *via* paper hard-copy or electronically using Research Electronic Data Capture (REDCap), a secure, online HIPAA-compliant survey tool (Harris et al., 2009). The RA asks study participants to complete questionnaires in-person during clinic visits, *via* email, or over the telephone if necessary.

Socio-demographic characteristics: Participants self-report their gender, race, ethnicity, marital status, education level, employment status, income, and frequency of technology use on a demographic questionnaire.Quality of life: Functional Assessment of Cancer Therapy-Lung (FACT-L; Cella et al., 1995). The FACT-L consists of four subscales assessing physical, social, emotional, and functional wellbeing during the past week. The instrument also contains the Lung Cancer Subscale (LCS), which evaluates specific symptoms related to lung cancer. Scores range from 0 to 5 on each item and the total scale score ranges from 0 to 136 with higher scores indicating better QOL.Symptoms: MD Anderson Symptom Inventory (MDASI; Cleeland et al., 2000). The MDASI is a 19-item survey, which consists of two subscales to assess cancer-related symptom severity and interference with daily activities on a 0–10 scale, with higher scores indicating worse symptoms.Mood: Hospital Anxiety and Depression Scale (HADS; Zigmond and Snaith, 1983). The 14-item HADS includes two subscales that measure anxiety and depression symptoms in the past week. Scores range from 0 to 21 on each subscale, and a threshold of > 7 on either subscale indicates clinically significant anxiety or depression symptoms.Coping strategies: Brief COPE Questionnaire; (Carver et al., 1989; Carver, 1997). The Brief COPE consists of 28 items assessing diverse coping methods on 14 subscales (e.g., active coping, use of emotional support, positive reframing, acceptance, behavioral disengagement, denial, and self-blame). Each item is scored on a 4-point Likert scale, with each subscale ranging from 0 to 8. Higher scores indicate higher use of that coping strategy. To reduce participant burden, we modified the questionnaire to consist of 8 subscales (Hagan et al., 2017).Supportive care service use: The Supportive Care Service Use Questionnaire (SCSUQ) includes two items that measure a patient’s use of mental health services, integrative medicine interventions, palliative care, and spiritual support over the past month.Mobile App Usability (intervention group only at week 12): The System Usability Scale (SUS; Bangor et al., 2008). The 10-item SUS evaluates patients’ subjective assessment of a product’s usability and acceptability.Perceptions and satisfaction with the mobile app (up to 30 intervention participants): Using a semi-structured qualitative interview guide, we assess patients’ experiences and satisfaction with the mobile app intervention.

#### Electronic health record review

2.3.4.

Study staff collects data from the electronic health record regarding patient age, cancer diagnosis, ECOG performance status, cancer therapy information, emergency department visits, hospitalizations, hospice referral, and use of supportive care services.

### Data analysis

2.4.

We will first report baseline characteristics of all study participants using descriptive statistics. The primary endpoint of the proposed study is feasibility. To assess intervention feasibility, we will calculate rates of patient enrollment, retention, intervention completion, and attrition while documenting reasons for withdrawal or loss to follow-up. The proposed intervention app will be deemed feasible if at least 65% of patients with advanced NSCLC who are approached to enroll in the study consent to participate and at least 70% complete the majority of study procedures as assigned (i.e., at least four of the six mobile app modules as well as baseline and 12-week outcome measures). These feasibility and intervention module completion thresholds are commonly used in behavioral intervention studies (Steinhauser et al., 2006; Siddiqi et al., 2008; Bowen et al., 2009). We will also use descriptive statistics to examine the acceptability and usability of the mobile app based on the System Usability Scale (Bangor et al., 2008).

To evaluate secondary outcomes, we will compare participant QOL (FACT-L; primary), symptoms (MDASI), mood (HADS), and coping (Brief COPE) between groups at week-12 using separate linear regression models controlling for the respective baseline values of the outcome variables. If necessary due to any imbalances between groups in baseline characteristics, we will control for selected demographic and clinical factors when examining the outcomes of interest. We will also test for potential moderators of the intervention effects using interaction terms for the linear models to assess whether differences in patient-reported outcomes are moderated by any clinical or socio-demographic factors (e.g., patient age, gender). Given the pilot nature of this study, we will use conservative (alpha = 0.05) and liberal (alpha = 0.15) values to assess statistical significance, especially as we evaluate outcomes in preparation for powering a subsequent full-scale efficacy trial. We will track and record reasons for all missing data (e.g., disease worsening, hospitalizations, hospice referral, lost to follow up, etc.). To address any missing data concerns, we will employ multiple imputation if data appear to be missing at random. If data are not missing at random, we will employ pattern mixture modeling.

Lastly, we will analyze the qualitative data with a multi-step process using coding and content analysis to explore patients’ perceptions and satisfaction regarding the mobile app content and features. This process will involve coding to structure data into categories and creating groups according to the broader issues or themes. We will identify major and minor themes within each content area, and we will extract and highlight messages. Two independent coders will examine discrepant, unexpected, or unclear data until agreement is reached. To assure the trustworthiness of our findings, we will take steps to maximize reliability and credibility including investigator triangulation (using a multidisciplinary team of investigators) and team debriefs of the interview content.

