## Abstract

Patients with advanced non-small cell lung cancer (NSCLC) often experience burdensome symptoms, emotional distress, and poor quality of life (QOL). While national guidelines recommend early palliative care to address these supportive care needs, most patients with advanced NSCLC lack access to such comprehensive care. Our aim in the current study is to test a novel model of palliative care delivery and use of innovative technology to evaluate the feasibility, acceptability, and preliminary efficacy of a supportive care mobile application (app) for improving symptom management and adaptive coping in patients with advanced NSCLC. We will enroll 120 patients with unresectable Stage III or IV NSCLC diagnosed within the past 12 weeks receiving care with palliative intent at a major academic comprehensive cancer center and its community affiliates. The study will take place in two phases, the first of which will be dedicated to adapting an evidence-based, early palliative care treatment guide and prior supportive care mobile app intervention to address the specific symptom management and coping needs of patients with advanced NSCLC. The second phase of the study will be a two-group, randomized controlled trial. Study patients will complete baseline self-report measures of symptoms, mood, coping skills, and QOL, after which they will be randomized to receive either the mobile app intervention combined with usual oncology care or usual oncology care alone. Intervention patients will use a tablet computer to self-administer the mobile app, which consists of six modules that teach evidence-based skills for managing burdensome symptoms and coping effectively with advanced cancer and its treatment. At 12 weeks follow up, patients in both groups will repeat the same self-report measures. We will use descriptive statistics to determine feasibility metrics of enrollment and retention rates. For secondary self-report measures, we will use linear regression controlling for baseline values. The results of the present study will contribute to a growing body of evidence regarding the supportive care needs of patients with advanced cancer and will have implications for how best to use innovative technology to widely disseminate comprehensive supportive care services to all patients who may benefit.

**Clinical Trial Registration:** [www.ClinicalTrials.gov], identifier[NCT04629300].

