Physical Domain (“Health”)	Identify and evaluate symptoms Learn to communicate effectively with oncology team about symptoms Apply helpful self-management strategies for coping with symptoms
Social Domain (“Relationships”)	Clarify types of social support needs related to coping with cancer Identify those who can help meet those needs Learn effective communication skills to ask others for help
Emotional Domain (“Emotions”)	Identify the range of cancer-related worries and emotions Practice skills for coping with uncertainty about the future Learn to overcome avoidance behaviors and to foster positive emotions
Functional Domain (“Lifestyle”)	Identify patterns in energy and stamina during treatment Practice skills for managing energy fluctuations and improving self-care Learn to prioritize and pace activities as needed to achieve valued life goals
Existential Domain (“Reflection”)	Reflect on life history, relationships, and goals Participate in activities that increase meaning and purpose in life despite cancer Learn to talk with the oncology team about how to prepare for the future

The second phase consists of a multi-site pilot randomized controlled trial in a sample of 120 patients with advanced NSCLC to assess the feasibility, acceptability, and preliminary efficacy of the THRIVE mobile app intervention for improving patient-reported symptoms, coping, and QOL compared to usual oncology care. Enrolled patients are randomized in 1:1 fashion and stratified by study site (i.e., Massachusetts General Hospital [MGH] Cancer Center, Dana-Farber Cancer Institute, and four community affiliates) to receive either the THRIVE mobile app combined with usual oncology care or usual oncology care alone. After enrollment, participants complete baseline self-report measures regarding their symptoms, mood, coping behaviors, and QOL, which they repeat at 12 weeks post baseline. We also conduct qualitative exit interviews with up to 30 patients who are randomized to the mobile app intervention to understand and assess patients’ experiences using the THRIVE app.

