#### Registration and randomization

2.2.2.

Enrolled patients are registered in the Clinical Trials Management System, OnCore, as required by Dana-Farber/Harvard Cancer Center standard operating procedures. Once the patient has been registered, a member from the MGH Cancer Outcomes Research and Education Program (independent from the study staff) performs randomization procedures using a predetermined computer-generated randomization schema developed and stored independently from the study team with 1:1 allocation, stratified by study site. Given the interventional nature of the study, neither participants nor study staff are blinded to group assignment.

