#### Usual oncology care group

2.3.2.

Patients assigned to the usual oncology care group receive standard cancer care without the THRIVE mobile app. As part of usual care, we query the electronic health record to track and record participant use of any supportive care services, such as social work, psychology, psychiatry, and palliative care. While we expect the referral and use of these services to be low and balanced between study groups, we will include these variables as covariates in the outcome analyses as needed.

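### Randomisation is stratified by site, but the secondary-outcome models omit site and add other covariates only when baseline imbalance is observed

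*Protocol article*

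**What the plan says.** The Design section states "Enrolled patients are randomized in 1:1 fashion and stratified by study site" and lists two cancer centres and four community affiliates. The Registration and randomization section repeats this: "with 1:1 allocation, stratified by study site". No other stratification factor is named.

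For the secondary outcomes (FACT-L first, then MDASI, HADS and Brief COPE), the Data analysis section specifies "separate linear regression models controlling for the respective baseline values of the outcome variables". The Abstract agrees: "we will use linear regression controlling for baseline values". Site appears in no model.

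The Data analysis section then gives a rule for further covariates: "If necessary due to any imbalances between groups in baseline characteristics, we will control for selected demographic and clinical factors". It names neither the factors nor a criterion for imbalance. The section on the usual care group has a second conditional rule, for use of supportive care services: "we will include these variables as covariates in the outcome analyses as needed".

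The primary endpoint is feasibility, judged against thresholds of 65% consent and 70% completion. The Power analysis section says the outcome data are to supply effect sizes for planning later trials.

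**The concern.** Stratified randomisation balances the arms within site, so between-site differences largely cancel out of the comparison of arms. A model without site does not know this. It leaves the between-site variation in the residual and reports a standard error larger than the design warrants. Some of the precision that stratification bought is then lost.

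The imbalance rule has a different fault. If a covariate predicts the outcome with coefficient b and the arms differ on it by d, the unadjusted effect is shifted by b times d. The rule looks only at d. A variable that is imbalanced but unrelated to outcome would be added for nothing, while a strongly prognostic variable that happens to be balanced would be left out, although it would have improved precision. Because neither the factors nor the trigger is defined, two analysts following the text could report different effects from the same data.

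At stake are the effect estimate and residual variance for FACT-L and the other self-report outcomes, which the protocol intends to carry forward into the design of a full-scale trial.

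**Working it through.** **1. The plan's own figure.** With 120 randomised and 10% attrition, 108 are analysed, 54 per arm. Power for 0.54 SD, two-sided 5%: 0.54 / sqrt(2/54) = 2.806, and Phi(2.806 - 1.960) = 80.1% (79.4% with the noncentral t). The stated 80% reproduces. It is an unadjusted two-mean calculation, so the covariate question does not change it.

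**2. Inputs for the site question.** From the protocol: 1:1 allocation, stratification by site, two centres and four affiliates, 108 analysed. Assumed, because the protocol gives no figures: baseline-outcome correlation r = 0.5; site share s of outcome variance 0.05 or 0.10; each affiliate its own stratum; site sizes 40/32/12/12/12/12.

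**3. Site differences that arise only after baseline.** Set the outcome variance to 1. After baseline adjustment, 1 - 0.5^2 = 0.75 remains.
- Within-site variance: W = 0.75 - s.
- Fraction of the site variance seen within one trial: f = 1 - (40^2 + 32^2 + 4 x 12^2)/120^2 = 1 - 3200/14400 = 0.778.
- Residual variance without site: T = W + 0.778s.
- The standard error is too large by sqrt(T/W), so the effective critical value is 1.96 x sqrt(T/W).
- True standard error: sqrt(4W/108). Power is evaluated at an illustrative difference of 0.45 SD.

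| | s = 0.05 | s = 0.10 |
|---|---|---|
| W; T | 0.700; 0.739 | 0.650; 0.728 |
| sqrt(T/W) | 1.027 | 1.058 |
| Effective critical value | 2.014 | 2.074 |
| Type I error without site | 4.4% | 3.8% |
| True standard error | 0.1610 | 0.1552 |
| Power with site | Phi(2.795 - 1.960) = 79.8% | Phi(2.900 - 1.960) = 82.6% |
| Power without site | Phi(2.795 - 2.014) = 78.3% | Phi(2.900 - 2.074) = 79.6% |
| Power lost | 1.5 points | 3.1 points |

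This assumes exact balance within site and ignores the degrees of freedom that site uses. Simulated trials with the same sizes, blocks of 4 and 10% random dropout gave type I error without site of 5.0% and 4.4%, and power of 77.5% against 78.8% and 78.8% against 82.0%. Monte Carlo error for the type I figures is sqrt(0.05 x 0.95/6000) = 0.28 points. The same runs gave 5.7% and 5.8% with site included, where the test is exact at 5%, so the 5.0% and 4.4% are probably a little high too. With site sizes 36/30/14/12/8/8, type I error without site was 3.8-4.9% and the gain from adding site was 2-4 points.

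**4. Site differences already present at baseline (patient mix).** The baseline score then carries much of the site effect. At the same shares, with r = 0.5 and sizes 36/30/14/12/8/8, type I error without site is about 4.4-5.0% and adding site gains under 1 point of power. At 0.54 SD, power is 90.3% either way for a 5% share, and 90.7% against 91.2% for 10%.

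**5. The imbalance trigger.** The protocol sets no threshold, so one was assumed: eight independent covariates, each added if its baseline difference has p < 0.10. By chance alone at least one enters in 1 - 0.90^8 = 57% of trials (56-58% simulated). Type I error of the resulting model is 5.3%, 4.5% and 3.7% when the eight together explain 5%, 15% and 30% of outcome variance. If both the unadjusted and the selected model were run and the more favourable one reported, it would be about 6.1-6.2%.

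**The case against.** The strongest reply has four parts.

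- **The error is small and in the safe direction.** This stands. Omitting a balanced stratification factor leaves the estimate unbiased and makes the test conservative. If site differences are mostly patient mix, the baseline score already in the model removes most of the problem.
- **Only secondary outcomes of a pilot are touched.** This also stands. No regression enters the 65% and 70% feasibility thresholds.
- **An article may leave covariates to the full protocol or SAP.** This stands in part. Silence about site alone would be no finding, and the text does not say that the baseline score is the only covariate. But the article does state a model and a rule for extending it, and that rule is unsound as written. Reading site into the clinical factors does not help: it would then enter only if imbalanced, which stratification is meant to prevent.
- **The trigger does little harm to the error rate.** If applied mechanically, this is so (3.7-5.3% under the assumed threshold). The fault is that the criterion does not measure prognostic value and that the choice is left open.

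A reader might go further and infer that covariates will be chosen with the outcomes in view. The text ties the choice to baseline characteristics and does not say when it is made. Unblinded study staff and two significance levels ("conservative (alpha = 0.05) and liberal (alpha = 0.15) values to assess statistical significance") leave room for this but do not show it. Nor should one quote 1 - 0.95^10 = 40% as the chance that the rule is triggered: the plan states no p < 0.05 screen, and items such as education, income and employment are not independent.

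**Conclusion.** The point holds at minor to moderate severity. The stated secondary-outcome models do not reflect the stratified design, and the rule for extending them uses the wrong criterion.

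For a site share of 5-10% and a baseline correlation of 0.5, the cost of omitting site is a type I error of about 4-5% at nominal 5% and a power loss of under 1 to about 4 points. Where in that range it falls depends on whether sites differ already at baseline or only afterwards, which the documents do not settle. The site sizes, and the treatment of each affiliate as a separate stratum, are also assumptions.

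The trigger has no single figure attached because the plan gives no threshold. Its consequence is that the reported effect depends on a covariate set not fixed in advance. The documents do not support reading this as an inflated type I error from omitting site, a biased estimate, a faulty power calculation or a threat to the feasibility conclusion.

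**What to change.** State one model for every self-report outcome: week-12 score on arm, baseline score and the site strata as used in randomisation, with small affiliates combined if needed. Name any additional prognostic baseline covariates before outcome data are examined. Delete the imbalance trigger and report baseline differences descriptively only. Replace the as-needed wording for supportive care use in the same way, with a statement fixed in advance of whether and how it enters.

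The cost is wording, plus at most five degrees of freedom for six sites, out of 108 - 3 = 105 in the current model. Fewer are used if affiliates are combined. Site is already recorded for randomisation, so no new data, patients or procedures are needed.

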##### Inclusion criteria

2.2.1.1.

Age ≥ 18 years.Diagnosed with unresectable Stage III or IV NSCLC in the past 12 weeks and receiving care with palliative intent.Eastern Cooperative Oncology Group (ECOG) Performance Status = 0–2 (with 0 indicating that the patient is asymptomatic, 1 that the patient is symptomatic but fully ambulatory, and 2 that the patient is symptomatic but in bed < 50% of the day; Cella et al., 2022).Plan to receive oncology care at one of the participating study sites.Ability to read and respond to questions in English.

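### The missing-data method for FACT-L and the other week-12 scores depends on whether data look missing at random, which observed data cannot show; the rule states no exception for deaths

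*Protocol article*

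**What the plan says.** Section 2.4 (Data analysis) of the protocol article compares FACT-L, MDASI, HADS and Brief COPE between groups at week 12 with "separate linear regression models controlling for the respective baseline values of the outcome variables". FACT-L is marked as the lead outcome among these secondary measures.

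The missing-data rule follows in the same section and has three parts:

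- Recording: "We will track and record reasons for all missing data (e.g., disease worsening, hospitalizations, hospice referral, lost to follow up, etc".).
- First branch: "To address any missing data concerns", "we will employ multiple imputation if data appear to be missing at random".
- Second branch: "If data are not missing at random, we will employ pattern mixture modeling".

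No criterion is given for deciding which branch applies, and neither method is named as primary or as a sensitivity analysis.

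Three other places bear on the rule:

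- Section 2.1 (Design) gives a single post-baseline assessment: patients complete baseline measures, "which they repeat at 12 weeks post baseline".
- Section 2.2.1.1 (Inclusion criteria) defines the population: "Diagnosed with unresectable Stage III or IV NSCLC in the past 12 weeks and receiving care with palliative intent".
- Section 2.3.4 (Electronic health record review) lists, besides age, diagnosis, ECOG status and cancer therapy, "emergency department visits, hospitalizations, hospice referral, and use of supportive care services". Death is not on that list.

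**The concern.** The article states a decision rule, so this is not a detail left to a statistical analysis plan. The difficulty is that the rule turns on a condition nobody can check. Data can give evidence against missing completely at random. Whether the unseen scores differ from the seen ones, after allowing for everything observed, is exactly what the data do not contain.

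Three features of this trial sharpen the problem:

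- With one follow-up assessment, a patient who misses week 12 leaves no earlier follow-up score that could show a decline.
- Disease worsening, hospitalization and hospice referral are plausibly tied to the week-12 quality of life that goes unrecorded, so MAR is doubtful from the start.
- The choice falls after the data are in, and section 2.2.2 says that study staff are not blinded to group. The article does not say whether the analyst is.

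The stake is the FACT-L group difference. Section 2.4.1 (Power analysis) intends the trial to supply effect sizes for powering later trials, so a biased estimate would carry into the next sample size. If the MAR branch is taken, the text plans no check on departures from it. Patients who die before week 12 are a separate matter: their score is not unrecorded but does not exist, and the rule does not set them apart.

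**Working it through.** **1. The plan's own figure.** Inputs from sections 2.1 and 2.4.1: 120 patients, 1:1, 10% attrition, 80% power, 0.54 SD. Two-sided alpha 0.05 is assumed, since the article does not state sidedness.

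- Evaluable: 120 × 0.90 = 108, or 54 per arm.
- Detectable difference: (1.96 + 0.84) × √(2/54) = 0.539 SD. Power at 0.54 SD is 0.801 by the normal approximation and 0.794 by the t-test.

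The power statement reproduces, and the point made here does not affect it.

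**2. Can the data show which branch applies?** Assumed set-up, not from the article: one million simulated patients, a baseline to week-12 correlation of 0.5, and about 10% missing at week 12 with a probability that depends on baseline only. The unseen scores were then lowered by 0 (MAR), 0.5 or 1.0 SD (both MNAR).

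| Shift in unseen scores (SD) | Missing share | Observed mean | Observed SD | Observed correlation | True overall mean |
|---|---|---|---|---|---|
| 0 | 0.103 | 0.031 | 0.996 | 0.494 | 0.001 |
| 0.5 | 0.103 | 0.031 | 0.996 | 0.494 | -0.051 |
| 1.0 | 0.103 | 0.031 | 0.996 | 0.494 | -0.102 |

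Everything an analyst could look at is the same in all three rows, while the true mean moves by about 0.10 SD. This follows from how the shift is built and holds at any sample size.

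**3. What is at stake if MAR imputation is used and MAR is wrong?** Let m be the missing fraction in an arm and δ the amount (in SD) by which its unseen scores fall below their MAR prediction. Imputation under MAR sets that arm's mean too high by m × δ, so

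bias in the group difference = m(app) × δ(app) − m(control) × δ(control).

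The article gives no δ and only one missing fraction, 10%. All values of δ are assumptions.

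| Situation | Calculation | Bias (SD) | Share of 0.54 SD |
|---|---|---|---|
| Both arms alike: 10% missing, any common δ | 0.10δ − 0.10δ | 0 | 0% |
| 10% missing, δ = 0.3 in one arm only | 0.10 × 0.3 | 0.03 | 6% |
| 10% missing, δ = 0.5 in one arm only | 0.10 × 0.5 | 0.05 | 9% |
| 10% missing, δ = 1.0 in one arm only | 0.10 × 1.0 | 0.10 | 19% |
| δ = 0.5 in both arms, 15% against 5% missing | 0.5 × (0.15 − 0.05) | 0.05 | 9% |

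A departure confined to the app arm flatters the app; one confined to the control arm works against it. For scale, the standard error of an unadjusted group difference with 54 per arm is √(2/54) = 0.19 SD, so 0.05 SD is about a quarter of a standard error.

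**4. Deaths.** The article gives no expected mortality and does not split the 10% attrition by cause, so the number of deaths before week 12 cannot be computed.

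**The case against.** The best defence is that the rule is more careful than many. It names two respectable methods and collects reasons for missingness prospectively, so the judgement need not rest on outcome values alone. It also concerns secondary outcomes of a pilot. Much of this stands. The recorded reasons do inform the choice, and at the planned 10% the bias is small beside the sampling error. They still cannot establish MAR, and a conditional choice gives the reader one answer where two would show how much the assumption matters.

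Four stronger readings are tempting, and the document does not support them:

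- **That the plan would impute quality of life for patients who have died.** It nowhere says so. Deaths might be judged not MAR and go to the second branch, or be dealt with in the full protocol, which is not shown. The list of reasons is open-ended and covers all missing data, so death may well be recorded. What can be said is that the rule, as stated, makes no exception for deaths.
- **That only one analysis will be run.** The two methods are written as alternatives, but further sensitivity analyses are not excluded.
- **That 30% missing FACT-L is tolerated because 70% completion is the feasibility threshold.** That threshold is a composite of four of six modules plus both assessments. A patient can fail it on modules and still supply a week-12 FACT-L, so it is no forecast of missing scores.
- **That some given share of the losses will be deaths.** No figure in the article supports any share.

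**Conclusion.** The point holds in a limited form. The rule makes the analysis of FACT-L and the other week-12 scores depend on a condition that cannot be verified, leaves the choice until the data are seen, and commits to no check of the assumption if MAR is adopted. It is also silent on deaths in a population where death before week 12 is plausible.

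The size rests on assumed departures. The bias is zero if missingness and departure are equal in the two arms. It is 0.05 SD, 9% of the 0.54 SD planning difference, if 10% are missing and a 0.5 SD departure occurs in one arm only, with a range of 0.03 to 0.10 SD for departures of 0.3 to 1.0 SD. Unequal missingness is possible because only one arm has app tasks, but the article gives no figure for it.

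The primary feasibility endpoint is untouched. What is affected is the lead efficacy estimate of a pilot and its use in planning the next trial. The change is worth making because it is cheap and uses methods already named in the plan.

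**What to change.** Replace the conditional rule in section 2.4 with a fixed one:

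1. Name multiple imputation under MAR as the single primary approach for the week-12 scores. Use baseline scores and health-record variables already collected (ECOG status, hospitalizations, hospice referral) in the imputation model. When only the week-12 score is missing, imputing from arm and baseline score alone adds little to the planned regression on complete cases; the extra variables are what make MAR more credible.
2. Run a delta-adjusted pattern-mixture analysis by arm as a planned sensitivity analysis in every case, whatever the data look like. Fix the range of δ before outcomes are seen, and include departures in one arm only.
3. State that scores missing because of death are not treated as ordinary missing data, and report deaths by arm beside the quality-of-life result. The investigators should say which quantity is then being estimated: an analysis among patients alive at week 12 conditions on an event after randomization, and is one choice among several.

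The cost is slightly more analysis work and agreement on a δ range. No new questionnaire or visit is needed. At most, one vital-status item is added to the health-record review if death is not already captured among the reasons for missing data.
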